## Abstract

**Background:**

Hyperglycaemia is common in intensive care units (ICUs), with a prevalence of up to 86.2%, increasing mortality. Technology has evolved towards continuous glucose monitoring (CGM), and its use in ICUs began especially during the coronavirus pandemic (COVID‐19). Various studies have evaluated the reliability of CGM, indicating that it is safe for use in critically ill patients.

**Aim:**

The aim of this study was to compare the use of CGM with point‐of‐care glucose (POC‐G) testing in ICU. Specific objectives include evaluating the glycaemic control, the frequency of POC‐G measurements, the incidence of hyperglycaemia, hypoglycaemia and morbidity and mortality at 90 days.

**Study Design:**

An experimental, controlled and randomized clinical trial with a single‐blind design will be conducted at Hospital Clinic of Barcelona (HCB). A sample size of 376 participants will be recruited and randomly assigned to two groups: an experimental group, where glycaemic management will be based on CGM; and a control group, where glucose will be managed through POC‐G testing, with a blinded CGM.

**Results:**

The primary variable considered will be time in range (TIR), with secondary outcomes including, time above range (TAR), time below range (TBR), number of POC‐G measurements, incidence of hyperglycaemia and hypoglycaemia, and mortality. Hypothesis testing will use the Kolmogorov–Smirnov test to assess data normality, with appropriate statistical tests applied, considering a *p*‐value <.05.

**Relevance to Clinical Practice:**

The results obtained will help us understand the impact of CGM on critically ill patients. CGM could potentially reduce the workload of nurses and improve the efficiency of decision‐making by the ICU team, enabling early identification and treatment of glucose complications, thereby enhancing safety. Patient safety, a reduction in patient fingerstick and a decreased care burden are the criteria that add value to this research.

What is known about the topic
Hyperglycaemia is prevalent in intensive care units (ICUs), affecting up to 86.2% of patients and increasing mortality risk.Continuous glucose monitoring (CGM) technology has advanced, especially during the COVID‐19 pandemic, and has been evaluated for reliability in critically ill patients.Although CGM shows promise in improving glycaemic control and reducing invasive blood tests, existing studies are limited by small sample sizes and during the COVID‐19 pandemic.
What this paper adds
Further evaluation of CGM's impact in critically ill ICU patients is necessary, requiring more clinical trials.This study will compare the effectiveness of CGM with point‐of‐care glucose testing in managing glucose levels in an ICU setting.It aims to assess whether CGM can better manage glycaemia, reduce hyperglycaemia and hypoglycaemia episodes, and improve outcomes such as morbidity and mortality within 90 days post‐ICU discharge.The research seeks to provide evidence supporting CGM as a standard ICU practice, potentially reducing health care provider workload and enhancing patient safety.

## BACKGROUND

1

The care of critically ill individuals has undergone a substantial transformation; intensive care units (ICUs) have evolved into highly specialized facilities.^1^

Critically ill patients exhibit blood glucose levels >180 mg/dL (10 mmol/L)^2^ with a prevalence of 77.8%–86.2%,^3^, ^4^ all contributing to heightened morbidity, mortality and safety concerns.^5^, ^6^, ^7^

The gold standard for ICU care is capillary blood glucose measurement, but there are instances where arterial blood or central venous blood samples are employed. These diverse approaches fall under the category of point‐of‐care glucose (POC‐G). Critically ill patients require three to six POC‐G measurements per day. In cases of intravenous insulin infusion, the frequency of POC‐G measurements may increase.^2^

Glucose control technology has advanced to continuous glucose monitoring (CGM), offering frequent measurements and their trends. Although CGM holds theoretical promise in improving hypoglycaemia detection and management compared with traditional POC‐G, it is important to note that it has not received approval from the U.S. Food and Drug Administration for inpatient use. However, during the COVID‐19 pandemic, the first studies appeared indicating that CGM can significantly enhance glycaemic management.^2^ CGM systems offer the opportunity to remotely monitor patients, providing alerts and the chance to prevent hypoglycaemia.^8^, ^9^

During the COVID‐19 pandemic, Agarwal et al. emphasized the feasibility, acceptability and reliability of CGM as a complementary measurement to POC‐G testing. A notable decrease in the frequency of POC‐G measurements, up to 71%, was observed when CGM was employed.^10^, ^11^, ^12^, ^13^, ^14^, ^15^

For CGM to be commercialized for people with diabetes in outpatient settings, a mean absolute relative difference (MARD) of less than 10% is required.^16^ However, in the ICU, an MARD below 15% is considered accurate, although a consensus is needed. Additionally, the Clarke Error Grid requires 98% of values to fall within zones A and B.^17^

Analysed articles found that CGM is accurate in ICUs with an MARD of 9.3%–13.9%, even during extracorporeal membrane oxygenation.^12^, ^13^, ^14^, ^18^, ^19^, ^20^, ^21^ The Clarke Error Grid results showed that 98.0%–99.7% of CGM readings fell within safe zones.^13^, ^14^, ^19^

Effective glycaemic control is indicated by a time in range (TIR) above 50% and a time below range (TBR) of less than 1%.^22^ Some authors reported a TIR of 46.1%–72% with a TBR of 0.25%–0.6%, reflecting excellent control and minimal hypoglycaemia.^10^, ^12^, ^13^, ^15^, ^23^

Although the results are promising, larger randomized controlled trials are needed to confirm the observed benefits.

## AIMS

2

We aimed to compare the use of CGM with POC‐G in the ICU. Specific objectives include glycaemic control, frequency of POC‐G measurements, incidence of hyperglycaemia, hypoglycaemia, morbidity and mortality at 90 days.

## DESIGN AND METHODS

3

An experimental, prospective, controlled, randomized and single‐blind clinical trial will be conducted at HCB. Unblinding will be permitted in case of adverse effects. Recruitment will take place from June 2024 to June 2026. This protocol was developed in accordance with the Standard Protocol Items: Recommendations for Interventional Trials (SPIRIT)^24^ and the World Health Organization Trial Registration Data Set.^25^

### Setting and sample

3.1

HCB has 62 ICU beds and 47 intermediate care beds, totalling 109, distributed across 6 specialized ICUs, with an annual population of 13 262. The sample size was calculated using the approximation of two independent proportions via the GRANMO Sample Size Calculator (https://apisal.es/GRANMO). Accepting an alpha risk (*α*) of .05 and a beta risk (*β*) of .2 in a two‐tailed test, a sample size of 376 individuals is deemed necessary. The expected proportion for the control group in terms of TIR is 35%, while for the experimental group, it is assumed to be 50%. An estimated loss of 10% has been considered. The ARCSINUS approximation was used.

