#### Statistical inference

3.5.2

To demonstrate significant differences between the two groups concerning the specific variables posed, a statistical analysis will be performed. First, the normality of the data will be checked using the Kolmogorov–Smirnov test. Based on the results, the most appropriate statistical tests will be used. For all tests, a *p*‐value <.05 (less than the significance criterion, *α* = .05) will be considered, and a confidence level of 95% will be established.

Data will be analysed using JAMOVI (version 2.5.6 or higher). Descriptive statistics will be presented as mean ± standard deviation for continuous variables. Continuous variables expected to follow a normal distribution will be compared between groups using Student's *t*‐test, and analysis of variance (ANOVA) will be used when analysing more than two groups or independent variables. For continuous variables that do not meet the normality assumption, the Mann–Whitney *U* test will be applied, as it is suitable for non‐parametric data.

Categorical and count variables will be analysed with Fisher's exact test for proportion comparisons. For variables with high counts, Poisson regression will be employed to provide a more nuanced analysis.

Morbidity and mortality will be evaluated using Kaplan–Meier survival analysis to estimate event probabilities over time, with differences between groups assessed through log‐rank tests to compare survival curves. Additionally, the analysis will address missing data using multiple imputation techniques to ensure the robustness and reliability of the results.

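### The sample size of 376 comes from a two-proportions formula, while the primary variable, time in range, is a percentage measured on each patient, so the stated size and 80% power do not describe the primary comparison

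*Protocol article*

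**What the plan says.** The abstract of the protocol article (Results) sets the endpoint: "The primary variable considered will be time in range (TIR"), with no cut-off that would turn it into a yes/no outcome.

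Section 3.1 (Setting and sample) then gives the method: "The sample size was calculated using the approximation of two independent proportions via the GRANMO Sample Size Calculator". The effect is: "The expected proportion for the control group in terms of TIR is 35%, while for the experimental group, it is assumed to be 50" per cent. The error rates are an alpha risk "of .05 and a beta risk" "of .2 in a two‐tailed test, a sample size of 376 individuals is deemed necessary". Attrition is allowed for: "An estimated loss of 10% has been considered". The formula is identified: "The ARCSINUS approximation was used".

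Elsewhere the article treats TIR as a quantity measured on each patient. Section 3.3 (Intervention) describes a sensor value every 5 minutes, 288 a day. Section 3.5.1 lists TIR beside mean glucose, coefficient of variation and similar summaries. The Background uses TIR as a level: above 50% indicates effective control, and earlier studies reported 46.1% to 72%.

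Section 3.5.2 assigns tests by type of variable: "Continuous variables expected to follow a normal distribution will be compared between groups using" Student's t-test, with Mann-Whitney where normality fails. Fisher's exact test is for categorical and count variables. No test is assigned to TIR by name.

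**The concern.** A two-proportions formula needs no SD because a yes/no outcome's variance is fixed by its event rate. A patient's TIR can lie anywhere from 0 to 100%, and its spread between patients is a separate quantity that the mean does not determine. Entering 35% and 50% as event rates amounts to assuming that every patient is in range either all of the time or none of it.

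What is at stake is the stated justification for the trial's size. The article calls 376 patients necessary for 80% power at 35% against 50%. If TIR is analysed as a continuous variable, the number required and the power at 376 both depend on an SD that the article does not give. Some of these critically ill patients will enter on a relative's consent, so the reason for the number enrolled should be sound.

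**Working it through.** **Inputs.** From section 3.1: 35% and 50%, two-sided alpha 0.05, beta 0.20, 10% loss, arcsine approximation. From section 3.1.3: 1:1 allocation. Not in the article: an SD for TIR. SDs of 20 to 45 points are assumed below to show the range.

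**1. Reproduce 376.**
- h = 2·asin(√0.50) − 2·asin(√0.35) = 0.3047
- n per arm = 2 × ((1.960 + 0.842)/0.3047)² = 169.1
- allowing for loss: 169.1/0.90 = 187.9, so 188 per arm and 376 in total

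The arithmetic is right. The usual pooled two-proportions formula gives nearly the same (170 per arm, 378 in total). The stated size therefore comes from a yes/no model.

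**2. The SD this model implies.**
- control: √(0.35 × 0.65) = 47.7 points
- experimental: √(0.50 × 0.50) = 50 points
- pooled: √((0.35 × 0.65 + 0.50 × 0.50)/2) = 48.9 points

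For a variable confined to 0–100%, these are the largest SDs possible at those means.

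**3. The same 15-point difference as a difference in means.** n per arm = 2 × (2.8016 × SD/15)², rounded up and divided by 0.90 for the total. Power (t-test) and detectable difference are for 169 evaluable per arm; detectable difference = 2.8016 × SD × √(2/169) = 0.305 × SD.

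| Assumed SD (points) | n per arm, 80% power | Total after 10% loss | Power for 15 points, 169 per arm | Detectable difference, 80% power |
|---|---|---|---|---|
| 20 | 28 | 64 | >99.9% | 6.1 |
| 25 | 44 | 98 | >99.9% | 7.6 |
| 30 | 63 | 140 | 99.6% | 9.1 |
| 35 | 86 | 192 | 97.5% | 10.7 |
| 40 | 112 | 250 | 93% | 12.2 |
| 45 | 142 | 316 | 86% | 13.7 |

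**4. Where 169 per arm gives exactly 80%.** SD = 15/(2.8016 × √(2/169)) = 49.2 points. This is just above the 48.9 ceiling in step 2.

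**5. Mann-Whitney.** Under normality its efficiency relative to the t-test is about 0.955, so the detectable difference becomes 0.305/√0.955, about 0.312 SD. The change is small.

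**6. The responder reading.** Suppose 35% and 50% are shares of patients reaching some TIR target, tested by Fisher's exact test. Power by full enumeration is 82.1% at 188 per arm and 77.7% at 169 per arm.

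**The case against.** The strongest counter-argument is that a responder endpoint was intended. Section 3.1 speaks of an expected proportion, the Background gives a 50% threshold for TIR, and the full protocol, which is not shown, may state a cut-off. Nor does section 3.5.2 assign a test to TIR; t-test or Mann-Whitney follows only from its general rule for continuous variables. This stands as a reason for caution about what was meant. It does not rescue the paragraph: the 50% threshold is background and is not made an endpoint, and the article names TIR itself as primary. This is not an omission that a condensed article may leave to the full document, because the model is stated and does not match the variable.

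Four stronger readings are tempting, and the documents do not support them.
- *The trial is underpowered.* It is not, for a 15-point difference in means (steps 3 and 4).
- *The trial is several times too large.* That needs an SD near the low end of the assumed range. Wear is at most 10 days and stops at discharge, MRI or death, so some records may be short, which tends to widen the spread between patients. At SD 45 the requirement is 316, not far below 376.
- *Fisher's exact test cannot give 80% power at this size.* It gives 82.1% with all 376 analysed and falls to 77.7% only if the whole 10% is lost. The article plans intention-to-treat analysis and multiple imputation, so 169 per arm is the pessimistic case.
- *Readers could not tell what effect the result supports or excludes.* The observed difference and its 95% confidence interval show that, whatever formula set the size.

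**Conclusion.** The concern holds as a mismatch between the sample-size model and the primary variable. The calculation is arithmetically correct, but for a yes/no outcome that the article does not define. For TIR as a patient-level percentage, the claim that 376 patients are necessary for 80% power is unsupported.

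The direction of the error is known: it is conservative. The size of the excess is not known, because it rests entirely on the missing SD; the totals of 64 to 316 in the table are conditional on assumed SDs. The power figures also assume 169 evaluable patients per arm and comparison by t-test. Nothing here biases the estimated effect or inflates the type I error rate. The stated basis for the primary comparison is wrong as written and should be corrected, but the trial's ability to detect its 15-point target is not in doubt.

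**What to change.** Keep the total of 376 and rewrite the sample-size paragraph in section 3.1:
- Delete the two-proportions derivation.
- State that the primary endpoint is mean patient-level TIR, and name the test for it.
- Cite a sourced SD for TIR and give the power for the protocol's own 15-point target with it.
- Give the detectable difference at 169 evaluable per arm (about 0.305 SD for a t-test, slightly more for Mann-Whitney), converted to points with that sourced SD. The SDs assumed in this review should not be written into the protocol.

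If a responder endpoint was intended, name it as primary, state its TIR cut-off, justify the 35% and 50%, and state power for the test to be used (for Fisher's exact test, 82% at 188 per arm and 78% if 10% are lost).

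The cost is one paragraph and a literature source for the SD. Recruitment does not change. The choice between the two endpoints should be recorded before any comparison of the groups.

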#### Participants

3.1.1

Recruitment will occur during the ICU stay. Potentially eligible patients will be identified by the nursing team. As appropriate, the researcher will provide written and verbal information about the study and invite the patient to ask questions. For patients unable to sign the informed consent, a family substitute will be approached.

#### Inclusion and exclusion criteria

3.1.2

Eligibility criteria include patients aged 18 years or over, having a stay in ICU and/or intermediate care, and having blood glucose levels >180 mg/dL (10 mmol/L). Exclusion criteria are pregnancy, individuals with contraindications for the use of CGM (such as skin issues or allergies to adhesives) and end‐of‐life process.

#### Randomization

3.1.3

Simple random probabilistic sampling will be done in a 1:1 ratio to the experimental (CGM) or control group (POC‐G), creating two parallel groups. To reduce bias and improve the enrolment, randomization will be performed at the bedside by the nurses responsible for the patients. In the ICUs of HCB, a random, opaque and sealed envelope will be selected, assigning the participant to the corresponding control or experimental group.

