#### Blinding

3.3.1

The patients involved in the study will be blinded, meaning they will not know whether they are in the experimental group using real‐time CGM or in the control group. The blinding process will be straightforward: both groups will have the same receiver and sensor inserted. In the experimental group, nurses will be able to see glucose values displayed on the receiver, while in the control group, the receiver will not show any values, effectively functioning as a ‘placebo’ sensor. This set‐up ensures that the patients cannot distinguish between the groups. Only the nurses will be aware of the group assignments, while the integrity of patient blinding is maintained.

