#### Control group

3.3.2

The CGM in the control group will be blinded, connected to the Dexcom G7 receiver to save the data, which will be downloaded later to the Clarity platform (Dexcom) for retrospective analysis.

POC‐G will be performed according to the usual protocol of TH. In case of glycaemic decompensation, POC‐G will be performed every 6 h and/or as needed. For patients with continuous intravenous insulin infusion, POC‐G may be performed every 2 h, 1 h or even every 15 min, depending on the stability of glucose levels and the nurse's judgement.

Therefore, there will be no intervention that modifies the usual treatment of patients in the ICU. The glucometer used in the centre is CareSens® Dual (Pascual y Furio Diabetes, Paterna, Valencia).

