### Ethical and research approvals

3.6

Ethics approval has been obtained from the Ethical Committee of HCB (Approval number: HCB/2023/0377) and the Bioethics Commission of the University of Barcelona (Institutional Review Board: IRB00003099/CER052429), covering all participating sites.

The devices and platforms used are validated with CE certification for use with people; however, they will be used in a different environment. Therefore, it will be reported to the Spanish Agency of Medicines and Medical Devices (AEMPS) via the NEOPS platform with No. 23‐0039. Informed consent will be obtained by the principal investigator, and the possibility of using the data for ancillary studies will be documented in the consent form.

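### Unblinded treating nurses allocate by an unordered pick of a sealed envelope, and no safeguard is described against discarding an opened envelope and drawing another

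*Protocol article*

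**What the plan says.** Section 3.1.3 of the protocol article names the method ("Simple random probabilistic sampling will be done in a 1:1 ratio"), the people ("randomization will be performed at the bedside by the nurses responsible for the patients") and the mechanism ("a random, opaque and sealed envelope will be selected, assigning the participant to the corresponding control or experimental group"). It gives reducing bias and improving enrolment as the reasons for having the treating nurses do this.

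Other sections describe what else these staff do:

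- **Screening** (3.1.1 Participants): "Potentially eligible patients will be identified by the nursing team".
- **Knowledge of the arm** (3.3.1 Blinding): "Only the nurses will be aware of the group assignments". The blinding applies to patients.
- **Discretion in care** (3.3.2 Control group): for patients on intravenous insulin infusion, the interval between point-of-care tests varies, "depending on the stability of glucose levels and the nurse's judgement". The number of such tests is a listed secondary outcome.

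Consent lies elsewhere. Section 3.6 (Ethical and research approvals) states: "Informed consent will be obtained by the principal investigator".

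The article mentions no numbering of envelopes, no order of opening, nothing written on an envelope before it is opened, no log and no custodian outside the care team.

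**The concern.** Concealment by envelope needs two things. The person allocating must not know the next assignment, and must not be able to change it once seen. Opacity and sealing serve the first. A fixed order with a record made before opening serves the second, because a skipped or discarded envelope then leaves a gap. A pick in no fixed order, as the text describes it, has no such sequence.

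This matters more here because one staff group screens, allocates and then treats with knowledge of the arm. Section 3.1.3 counts allocation by these nurses as a protection against bias, although keeping allocation away from treating staff is the usual protection. Section 5 (Limitations) attributes possible selection bias to random assignment itself, so the actual route to such bias is not recognised.

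If redraws depended on how the patient looked at the bedside, time in range, test counts and mortality would all be compared between groups formed partly by unrecorded judgement. The intention-to-treat rule in 3.4 would not help, because it would analyse the allocation that was kept. Adjustment for the covariates listed in 3.5.1 could not reliably remove selection on judgements that nobody recorded.

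**Working it through.** **1. The plan's own figure.** Section 3.1 gives 35% versus 50%, two-sided alpha 0.05, beta 0.2, the arcsine approximation and 10% loss.

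- h = 2·asin(√0.50) − 2·asin(√0.35) = 0.3047
- n per arm = 2(1.960 + 0.842)² / h² = 169.09
- 169.09 / 0.90 = 187.88, so 188 per arm and 376 in total

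The stated 376 reproduces and is used below.

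**2. What the safeguards in the text cover.**

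| Route to a chosen allocation | Covered in the text? |
|---|---|
| Reading the assignment before opening | Yes: opaque and sealed |
| The allocating nurse deciding consent | Largely: consent is obtained by the principal investigator |
| Opening one envelope, setting it aside and drawing another | Nothing described |

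**3. Would the final arm counts reveal redrawing?** Take each draw as an independent 1:1 assignment, as simple randomisation implies. With no redrawing, the CGM count is Binomial(376, 0.5), with a 95% range of 169 to 207. The chance that the arms differ by 40 or more is 0.044, so the chance of a CGM count above 207 is half of that, about 0.022.

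Now assume that a share r of first draws that fall to control is redrawn once. Half of these become CGM:

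P(CGM) = 0.5 + 0.5 × r × 0.5

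| r (assumed) | P(CGM) | Expected CGM count | Patients who change arm (count − 188) | P(count > 207) |
|---|---|---|---|---|
| 5% | 0.5125 | 192.7 | 4.7 | 0.06 |
| 10% | 0.525 | 197.4 | 9.4 | 0.15 |
| 20% | 0.55 | 206.8 | 18.8 | 0.47 |

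Even at 20%, the count stays within its limit more often than not.

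**4. Dependence on the model.** The text does not say whether the envelopes are independent assignments or a fixed stock. If the stock were 188 and 188 (an assumption) and unwanted envelopes went back into it, the final counts would be equal at full recruitment whatever had happened, and would check nothing. If unwanted envelopes were thrown away, only a count of the stock would show it.

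**The case against.** The strongest reply is that this is a condensed article. Numbering, custody and a log are commonly left to the full protocol, and the sentence on the envelope may simply be loosely worded. There are also real protections: opaque sealed envelopes, consent by the principal investigator, and participant codes 001 to 376 held by the principal investigator (3.4).

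Much of this stands. A reader might infer that allocation can be steered without trace, or that no record would show it. The article does not support that. It is silent on a log and nowhere says that envelopes may be returned. The protections narrow the risk mainly to redrawing or discarding after opening. Nor does the text suggest that nurses would do so, or in which direction. The redraw shares above are illustrations.

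A reader might also infer that leaving balance between units to chance is a serious fault, since the beds are "distributed across 6 specialized ICUs". That does not hold either. Simple randomisation is valid at 376. Using power = Φ(h/√(1/a + 1/b) − 1.96), power is 0.800 with 169 and 169 evaluable patients and 0.795 with 150 and 188, a loss of half a percentage point. An uneven split within one unit is not bias, and 3.5.1 already lists reason for admission and severity scores for consideration.

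The reply does not remove the point about the mechanism. The article states how an envelope is chosen, and what it states is not opening in order. That is wording to correct, not a detail left out.

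**Conclusion.** The point holds in a limited form. The stated mechanism leaves one route unguarded, redrawing after opening, in the hands of staff who also screen and treat unblinded, and the article calls this arrangement bias-reducing. The size of any resulting bias cannot be derived from the document. What can be shown is that final arm counts would be a weak check: about a 15% chance of crossing the upper limit of 207 if 10% of control draws were redrawn once, 6% at a share of 5%, and 47% at 20%. These figures rest on independent 1:1 draws, a single redraw and redrawing from control only, all of which are assumptions. The mechanism should be corrected. Nothing in the document shows that allocation has been compromised.

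**What to change.** In 3.1.3, replace the sentence on selecting an envelope with a procedure along these lines:

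- The allocation list is generated off-unit, and opaque sealed envelopes are prepared from it and numbered in sequence.
- Envelopes are opened strictly in order, after consent.
- Patient code, date and time are written on the envelope before it is opened.
- Existing study staff outside bedside care reconcile the stock against a log.

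Password-protected electronic allocation would serve equally well. Drop the statement that bedside allocation by the treating nurses reduces bias.

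Section 3 sets recruitment from June 2024 to June 2026. If it has begun, apply the procedure to the remaining participants and reconcile the envelopes already used against the patients enrolled. If the full protocol already contains these steps, the article's sentence should be brought into line with it.

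The cost is re-preparing the envelopes and keeping a log. The sample size does not change. Blocking or stratifying by ICU is optional. If chosen, varying block sizes would limit the predictability that blocks bring where staff know the arms.
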